### Statistical methods

2.7

We will use chi-square test or Fisher exact test to compare the difference of the categorical variables between the groups with complete repair and with partial repair. The continuous variables will be compared between the two groups by Mann-Whitney *U* test. In order to exam the reliability of the outcomes of ultrasound elastography (including color histograms of each color and SWV), intraclass correlation coefficients (ICC) will be used to evaluate the inter-rater reliability and intra-rater reliability. When it comes to the correlational analysis of the findings of ultrasound elastography and MRI, Spearman's rank correlation is used for 2 continuous variables, while Cramer's V correlation is used for one continuous variable versus one nominal variable. The predictive validity of ultrasound elastography for the reparability of large-to-massive RCTs will be analyzed by receiver operating characteristic (ROC) analysis to calculate the area under the curve (AUC). Finally, we will perform a logistic regression for the associations between the reparability and risk factors (such as age, sex, body mass index (BMI), inflammatory arthritis, the findings of ultrasound elastography, the findings of MRI). The statistical analysis will be performed using Stata 15 (StataCorp. 2017. Stata Statistical Software: Release 15. College Station, TX: StataCorp LLC.). A *P* value less than .05 will be defined as statistically significant.

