##### Image

2.5.2.1

(1)Ultrasound elastography: Physicians with at least 3-year experience of ultrasound will use Siemens Acuson S2000 ultrasound system (Siemens Healthcare, Erlangen, Germany) with a linear-array transducer with a bandwidth of 4 to 9 MHz to assess the middle third part of 2 rotator cuff muscles (supraspinatus muscle and infraspinatus muscle). The positioning of the ultrasound transducer is presented in Figure 1. The ultrasound transducer is perpendicular to the long axis of the muscle belly. The ultrasound elastography can evaluate the tissue quality by semiquantitative analysis and quantitative analysis.i.Semiquantitative analysis: Compressive ultrasound elastography will be used for the semiquantitative analysis. The pressure of the transducer on the skin should be controlled as the quality factor keeps at least 60 to achieve good color imaging.^[22]^ The region of interest (ROI) is located at the middle third part of each muscle. The software of ImageJ (Rasband, W.S., ImageJ, U. S. National Institutes of Health, Bethesda, MD, https://imagej.nih.gov/ij/, 1997–2018) is used to analyze the red pixels, green pixels, and blue pixels of the color histograms (each color pixels range: 0–255, with an accuracy of 0.1 pixel). The color pixels of each muscle will be the mean values of repeated measurements for 4 times.ii.Quantitative analysis: SWE will be used for quantitative analysis through the software of virtual touch tissue imaging quantification [VTIQ] (Siemens Healthcare, Erlangen, Germany). The ROI of each muscle will be separated into 4 quadrants. Our investigators will measure the SWV at the center of each quadrant for 4 times, and the SWV of each quadrant will be the mean value of these measurements. The unit of SWV is m/s with an accuracy of 0.01 m/s.iii.Test reliability: Twenty participants will be selected to test the reliability of color histograms of each color and SWV. Two physicians will perform the ultrasound elastography independently to test the inter-rater reliability. Besides, each physician will also repeat the exams at 2 separate time to test the intra-rater reliability.(2)MRI: MRI will be performed on a 1.5T system (Signa Horizon LX, GE Healthcare) equipped with a standard shoulder surface coil. The shoulder MRI protocol is identical for all patients and consisted of axial proton-density-weighted fast spin-echo with fat suppression sequence, the sequences is performed above the level of the acromioclavicular joint down to below the axillary pouch with the following parameters: Coronal oblique proton-density-weighted with and without fat suppression, with axis parallel to the supraspinatus tendon, and sagittal oblique proton-density--weighted with and without fat suppression, with axis perpendicular to the coronal oblique axis, the fast spin-echo sequences are performed with the following parameters: TR ms/TE ms, 2700–4800 /25–40, echo-train length, 6; matrix, 256 × 256; field of view, 180 mm; section thickness, 2.5 mm with 2-mm gap. No IV or intraarticular gadolinium is administered. A musculoskeletal radiologist will read the images and evaluate the size of tear, the degree of tendon retraction (Patte classification^[13]^), fatty infiltration of rotator cuff muscles (Goutallier classification^[11]^), and muscle atrophy (tangent sign^[12]^).

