### Sample size estimation

2.8

The sample size estimation for a ROC analysis will based on a research by Hanley et al.^[23]^ According to Iagulli et al,^[24]^ about half of large-to-massive RCTs can be completely repaired, so the ratio of partial repair cases to complete repair cases is supposed to be 1. Under the assumption of (1) type I error = 0.05 (2) type II error = 0.2 (3) acceptable discrimination is 0.7, the sample size should be 62 participants. The estimated sample size will be corrected to 78 participants in consideration of 20% drop-out rate.

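### Section 2.7 has no class for ordered variables, so the Patte and Goutallier grades would by natural reading be compared between repair groups without using their order, at some cost in power

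*Protocol article*

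**What the plan says.** Section 2.7 (Statistical methods) sorts variables into two classes for the comparison of complete with partial repair. For the first it states: "We will use chi-square test or Fisher exact test to compare the difference of the categorical variables". For the second: "The continuous variables will be compared between the two groups by Mann-Whitney *U* test". No ordinal class, trend test or rank test for grades is named.

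Section 2.5.2.1 (Image) lists what the radiologist reads on MRI besides tear size: "the degree of tendon retraction (Patte classification"), "fatty infiltration of rotator cuff muscles (Goutallier classification") and "muscle atrophy (tangent sign"). It does not give the number of levels of any of the three.

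The correlation plan in section 2.7 uses the same two-way split. Spearman's coefficient is for two continuous variables, and "Cramer's V correlation is used for one continuous variable versus one nominal variable". The significance rule is "A *P* value less than .05 will be defined as statistically significant".

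**The concern.** Patte and Goutallier grades are neither continuous nor nominal; they are degrees on an ordered scale. No sentence assigns them to a test. Under a two-class rule, however, they land with the categorical variables, and the reference to nominal variables in the correlation plan points the same way.

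Order matters because the protocol's own premise is directional. The Abstract and the Introduction both tie reparability to the degree of atrophy or fatty infiltration, with the poorest tissue being irreparable. A chi-square test on k grades spreads its power over k − 1 degrees of freedom, most of them describing patterns that this premise does not predict. At stake is whether a real association between an MRI grade and reparability is reported as non-significant in the table comparing the two repair groups.

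**Working it through.** **Inputs.** Section 2.8 gives "1) type I error = 0.05 (2) type II error = 0.2 (3) acceptable discrimination is 0.7", a 1:1 ratio of partial to complete repair, 62 participants, and 78 after a 20% drop-out allowance. The comparison is therefore 31 v 31. Assumed, because the article does not state them: 2 to 5 levels per finding, two-sided tests, and a null AUC of 0.5.

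**The plan's own figure.** With n per group, the Hanley-McNeil variance is

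V(A) = [A(1−A) + (n−1)(Q1−A²) + (n−1)(Q2−A²)] / n², where Q1 = A/(2−A) and Q2 = 2A²/(1+A).

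The requirement is 1.96·√V(0.5) + 0.8416·√V(0.7) ≤ 0.7 − 0.5 = 0.20.

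- n = 31: 1.96 × 0.0739 + 0.8416 × 0.0666 = 0.2009, just above 0.20.
- n = 32: 1.96 × 0.0727 + 0.8416 × 0.0655 = 0.1977, which meets it.

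This gives 64 in total, within 2 of the stated 62. The drop-out step is exact: 62 / 0.8 = 77.5, rounded up to 78. Both figures concern the ROC analysis and do not depend on how the MRI grades are tested.

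**Power, model A.** Proportional-odds shift, with the AUC of the graded finding itself (ties counted as half) set to 0.70; 31 v 31, 20,000 replicates. The range for 3 grades covers an even and a mildly skewed grade distribution; the other rows use an even one.

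| Levels | Pearson chi-square | Mann-Whitney, tie-corrected | Loss (points) |
|---|---|---|---|
| 2 | 91% | 91% | 0 |
| 3 | 76–78% | 84–86% | 8–9 |
| 4 | 67% | 83% | 15 |
| 5 | 60% | 82% | 22 |

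A skewed five-grade distribution gave 60% v 82% as well.

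**Power, model B.** Normal shift on an underlying continuous scale with AUC 0.70, then cut into grades; 3,000 replicates. Results were 63% v 73% (3 grades) and 54% v 77% (5 grades). A separate run at 31 v 31 and AUC 0.70 gave 64% v 72%, 60% v 75% and 56% v 78% for 3, 4 and 5 grades. Absolute power depends on the model; the gaps agree at 8 to 10, about 15, and 22 to 23 points.

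**Other effect sizes (model A, AUC 0.60 to 0.75).** The relative loss, (Mann-Whitney − chi-square) / Mann-Whitney, is 3–24% with 3 grades, 7–33% with 4 and 12–48% with 5.

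**Analytic check.** For a pure trend, 80% power on 1 df needs a noncentrality of (1.96 + 0.8416)² = 7.849. The same noncentrality gives 71%, 65% and 60% power on 2, 3 and 4 df. Restoring 80% would need 9.635, 10.903 and 11.935, that is, sample size ratios of 9.635/7.849 = 1.23, 10.903/7.849 = 1.39 and 11.935/7.849 = 1.52. Applied to 62, these are 77, 87 and 95. They show the scale of the loss; they are not a case for a larger study.

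**Type I error.** With 3 and 5 grades under no difference, chi-square rejects in 4.5–5.3% of runs and Mann-Whitney in 5.0–5.2%. The gain in power is not bought with false positives.

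**The reverse case.** With grade proportions of 20/60/20% in one group and 40/20/40% in the other, chi-square has 85% power and Mann-Whitney 6%.

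**The case against.** *The allocation is inferred.* The sentence on categorical variables is general and is right for sex, side of lesion and inflammatory arthritis. An article may also leave the handling of ordinal grades to a fuller document. The first part stands: that the grades go to chi-square is a reading, not a stated rule. The second has less force, because section 2.7 does fix the tests and the split, and its treatment of correlations supports the same reading.

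*Chi-square is a valid test and not without benefit.* This stands. Its error rate is near nominal, and it finds non-monotone differences that a rank test misses. The protocol hypothesises none, so the rank test fits better, but this is a better choice rather than the repair of an invalid one. Sparse cells are no separate fault, since Fisher's exact test is already offered. Fisher's test was not simulated; it too ignores order.

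*The size depends on unstated grade counts.* This stands. If patients with such large tears cluster in a few grades, the loss moves towards the smaller figures.

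*A stronger reading is tempting.* A reader might infer that elastography, tested by Mann-Whitney, is given an unfair advantage over MRI, tested by a weaker method. The documents do not support that. No planned analysis sets MRI against elastography through these P values. Elastography is judged by its AUC. MRI enters through correlations and as a candidate factor in the logistic regression, which gives a second look at MRI and reparability.

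**Conclusion.** The point holds as a cheap improvement. Section 2.7 lacks an ordinal class, and on the natural reading the Patte and Goutallier grades would be compared between repair groups by tests that ignore order, against a monotone premise. At 31 v 31 and AUC 0.70 the cost is roughly 8 to 10 percentage points of power with 3 grades, about 15 with 4 and about 22 with 5, and nil for a tangent sign recorded as present or absent. These figures assume the grade counts, a monotone shift between groups and two-sided tests at 0.05.

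The consequence is confined to a secondary group comparison. It would be wrong to conclude that the primary ROC analysis or the sample size of 62 (78 with drop-out) is affected.

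**What to change.** In section 2.7, add one sentence: Patte and Goutallier grades will be compared between complete and partial repair by the tie-corrected Mann-Whitney U test (or a Cochran-Armitage trend test), and chi-square or Fisher's exact test will be kept for binary and nominal variables, including the tangent sign if it is binary. No change to the coding of grades in the logistic regression is asked for, since the article does not fix that coding.

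The cost is one sentence: no extra data or participants, and Mann-Whitney is already in the plan. The small downside is little power against a non-monotone difference. Showing the full grade distribution in each repair group would let a reader see one.

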Recently, clinicians used the ultrasound to predict the reparability of RCTs, which was found to be related to the area of tears and age.^[15]^ Although this study included not only cases with large-to-massive RCTs, it was still the pioneer in this field of research. Rosskopf et al^[16]^ applied ultrasound shear wave elastography (SWE) to study the shear wave velocity (SWV) of supraspinatus muscles under different situations, including normal, tendinopathy, partial-thickness tear, and full-thickness tear. This research also studied the correlations between SWV of supraspinatus muscles and MRI findings, and SWV was correlated to the degree of tendon retraction and muscle atrophy of rotator cuff shown on the MRI. However, most of cases in this research was only less severe RCTs or even rotator cuff tendinopathy, and only small proportion of severely fatty infiltration was observed.

The primary objective of our study is to predict the reparability of large-to-massive RCTs using ultrasound elastography. Before the predictive validity of ultrasound elastography is measured, our investigators will assess the reliability of ultrasound elastography when administered to cases with large-to-massive RCTs, and we will check the correlations between the findings of ultrasound elastography and MRI.

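### Section 2.7 applies Cramer's V to ungrouped continuous elastography values against categorical MRI findings, where the coefficient is close to 1 with or without an association and its test almost never rejects

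*Protocol article*

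**What the plan says.** The Introduction of the protocol article sets, as a step before predictive validity is assessed, that "we will check the correlations between the findings of ultrasound elastography and MRI". Section 2.7 (Statistical methods) gives two rules for it. The first is that "Spearman's rank correlation is used for 2 continuous variables". The second is that Cramer's "V correlation is used for one continuous variable versus one nominal variable". There is no separate rule for ordered grades.

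The Image section (2.5.2.1) defines the variables. For shear wave velocity (SWV), "the SWV of each quadrant will be the mean value of these measurements", and "The unit of SWV is m/s with an accuracy of 0.01 m/s". Colour histograms run from 0 to 255 "with an accuracy of 0.1 pixel", and "The color pixels of each muscle will be the mean values of repeated measurements for 4 times". On the MRI side the radiologist records tear size, tendon retraction (Patte), "fatty infiltration of rotator cuff muscles (Goutallier classification") and muscle atrophy (tangent sign). The article states no cut-points or categories for any elastography value.

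**The concern.** Cramer's V rescales the chi-square statistic of a contingency table, so both variables must be categorical. If a finely recorded continuous value enters the table as it stands, nearly every participant gets a row of their own. V is then driven by the number of distinct values rather than by any relation with the MRI grade.

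Three of the four MRI findings are classifications, and the Spearman rule for continuous pairs does not cover them. The elastography side has 8 SWV values (4 quadrants x 2 muscles) and 6 colour values (3 colours x 2 muscles), 14 in all. With one reading per MRI classification that makes 14 x 3 = 42 affected pairs. Retraction, fatty infiltration and atrophy are the MRI features that the Introduction links to reparability, and the Discussion presents their relation to elastography as a result of the study. Under the stated rule these comparisons would yield a coefficient that cannot be interpreted, gives no direction, and ignores the order of the Patte and Goutallier grades.

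**Working it through.** **Inputs.** From section 2.8: 62 evaluable participants, 78 enrolled. From section 2.5.2.1: SWV to 0.01 m/s, colour to 0.1. Assumed, because the article does not give them: SD of SWV 0.3 to 1.0 m/s, SD of colour 5 to 20, MRI findings with 2, 3 or 5 categories, and the category shares.

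**1. The plan's own figure.** The article gives no figure for V, but its sample size sets the size of the table. Large-sample Hanley-McNeil variance at AUC A = 0.7:

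A/(2 - A) + 2A²/(1 + A) - 2A² = 0.5385 + 0.5765 - 0.98 = 0.1349.

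At AUC 0.5 the variance is 0.1667. With two-sided alpha 0.05 (sidedness is not stated) and power 0.80:

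n per group = (1.96 x √0.1667 + 0.842 x √0.1349)² / 0.2² = 30.8, so 31 + 31 = 62.

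Dropout: 62/0.8 = 77.5, so 78. Both stated figures reproduce.

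**2. No ties.** V = √[χ² / (n·min(r - 1, k - 1))], with r rows and k columns. If all n values are distinct, each row holds one participant. A participant in a column with total c contributes O²/E = n/c. Each column therefore sums to n, and all k columns to nk. Then χ² = nk - n = n(k - 1), and V = 1 exactly, whatever the data. The degrees of freedom are (n - 1)(k - 1). At n = 62, k = 2 this is χ² = 62 on 61 df, P = 0.44; at k = 5 it is 248 on 244 df, P = 0.42. Without ties, the P value carries no information either.

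**3. Ties from rounding, no association.** With r distinct values, the expected χ² is n(r - 1)(k - 1)/(n - 1), so V is about √[(r - 1)/(n - 1)] for r > k. The number of MRI categories cancels. Simulation, 1,000 data sets per setting:

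| n | Value | Mean distinct values | √[(r - 1)/(n - 1)] | Simulated mean V |
|---|---|---|---|---|
| 62 | SWV, SD 1.0 | 57.0 | 0.958 | 0.957 to 0.959 |
| 62 | SWV, SD 0.5 | 52.5 | 0.919 | 0.918 to 0.920 |
| 62 | SWV, SD 0.3 | 47.4 | 0.872 | 0.870 to 0.872 |
| 62 | Colour, SD 20 | 59.4 | 0.978 | 0.978 |
| 62 | Colour, SD 5 | 52.6 | 0.920 | 0.919 to 0.920 |
| 78 | SWV, SD 1.0 | 70.2 | 0.948 | 0.946 to 0.947 |
| 78 | SWV, SD 0.3 | 56.1 | 0.846 | 0.843 to 0.846 |

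The ranges in the last column run over 2, 3 and 5 categories. If the means are kept unrounded, V = 1.000 in every data set.

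**4. With an association** (n = 62, SWV SD 0.5 m/s, 5 ordered grades):

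| Latent correlation | 0 | 0.3 | 0.5 | 0.7 |
|---|---|---|---|---|
| Mean V | 0.921 | 0.920 | 0.922 | 0.932 |
| χ² test rejects | 0% | 0% | 0% | 0.1% |
| Mean Spearman rho | 0.00 | 0.27 | 0.46 | 0.66 |
| Spearman test rejects | 6% | 57% | 97% | 100% |

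At n = 78 the highest rejection rate of the χ² test is 0.9%, at latent correlation 0.7. In the same data a rank correlation separates the cases and V does not.

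**The case against.** The strongest reply is that V presupposes a contingency table, so the authors may intend to group the elastography values first, and cut-points may sit in a fuller protocol or analysis plan that is not shown. This stands as a limit on the consequence. If the values were cut into 2 to 4 groups, mean V under no association would be about 0.10 to 0.25 at n = 62, and the inflation would be gone. It does not rescue the sentence, which calls the variable continuous and states no grouping.

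It is also fair to say that section 2.7 names no MRI variable as nominal, so sending Patte and Goutallier to the V rule is an inference. The inference is reasonable, since the only other rule is for two continuous variables. The tangent sign, if read as present or absent, is the clearest case.

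A reader might go further in three ways that the article does not support:

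- *That every elastography-MRI correlation will come out near 1.* This needs ungrouped tabulation, and it does not touch MRI tear size, which goes to Spearman if kept continuous.
- *That noise would be declared significant.* The coefficient is inflated but its test is not. It almost never rejects, so at the 0.05 level the error is towards missed associations.
- *That the main result is compromised.* The ROC analysis, logistic regression, reliability coefficients, group comparisons and sample size do not use V.

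**Conclusion.** The Cramer's V rule is wrong as written for continuous elastography values against categorical MRI findings. Applied literally, it gives a mean V of about 0.85 to 1.00 at n = 62 to 78, almost the same with no association as with a strong one, with no direction and a test that has practically no power. The range rests on the assumed SDs; the value of exactly 1 without ties is algebra and rests on no assumption about spread. The result also depends on tabulating ungrouped values, which is the literal reading of the sentence.

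The damage is confined to a stated secondary step, the comparison of elastography with the Patte, Goutallier and tangent-sign readings. Because the primary analysis and the sample size stand, and the error can be corrected at analysis, this is a point that should be fixed rather than one that blocks the study.

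**What to change.** Replace the Cramer's V clause in section 2.7 as follows:

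- Elastography against the ordered Patte and Goutallier grades: Spearman's rho or Kendall's tau-b, with 95% CI.
- Elastography against the tangent sign, if read as present or absent: rank-biserial correlation (or, equivalently, the AUC), with 95% CI.
- Elastography against continuous MRI tear size: leave the existing Spearman rule in place.

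If grouping of the elastography values was intended, the text should say so and fix the cut-points before the data are analysed. The rank methods above avoid that choice.

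The cost is one sentence. No extra data, visits or participants are needed, and the methods are available in Stata 15, the package the plan already names.

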**Methods::**

This is a prospective observational study and participants with large-to-massive RCTs who are going to have surgeries will be included. Out investigators will evaluate the shoulder passive range of motion (ROM) and strength of all participants. Participants’ degree of shoulder pain and activities of daily living (ADLs) will be assessed by American Shoulder and Elbow Surgeons (ASES) score. The ultrasound elastography will be used to evaluate the tissue quality of supraspinatus muscle and infraspinatus muscle. To test the reliability of the ultrasound elastography, two physicians will perform the ultrasound elastography independently and twenty participants will be selected for the reliability test. Besides, MRI will be used to evaluate the size of tear, the degree of tendon retraction, fatty infiltration of rotator cuff muscles, and muscle atrophy. Finally, the orthopedic surgeons will perform surgeries and decide whether the teared stump can be completely repaired intraoperatively. The primary analysis is the predictive validity of ultrasound elastography for the reparability of large-to-massive RCTs. Before the predictive validity of ultrasound elastography is measured, our investigators will assess the reliability of ultrasound elastography when administered to cases with large-to-massive RCTs, and we will check the correlations between the findings of ultrasound elastography and MRI.

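### The primary ROC analysis names no primary elastography index among up to 14 and sets no multiplicity rule, although the sample size is for a single AUC

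*Protocol article*

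**What the plan says.** The Methods part of the abstract defines the primary question: "The primary analysis is the predictive validity of ultrasound elastography for the reparability of large-to-massive RCTs". Section 2.7 (Statistical methods) gives the method: "The predictive validity of ultrasound elastography for the reparability of large-to-massive RCTs will be analyzed by receiver operating characteristic (ROC) analysis". Neither place names a muscle, a colour, a quadrant or a composite.

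The Image part of section 2.5 shows how many numbers elastography produces:

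- Physicians scan "to assess the middle third part of 2 rotator cuff muscles (supraspinatus muscle and infraspinatus muscle".
- For compressive elastography, image software "is used to analyze the red pixels, green pixels, and blue pixels of the color histograms". Averaging is within muscle: "The color pixels of each muscle will be the mean values of repeated measurements for 4 times". That leaves one mean per colour per muscle.
- For shear wave elastography, each muscle's region of interest is split into four quadrants, and "the SWV of each quadrant will be the mean value of these measurements". No average over quadrants is defined.

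Section 2.7 also compares continuous variables between the complete-repair and partial-repair groups by the Mann-Whitney U test. It closes with one significance threshold, P below .05, for everything.

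Section 2.8 (Sample size estimation) assumes "1) type I error = 0.05 (2) type II error = 0.2", an AUC of 0.7 and a 1:1 ratio of partial to complete repair. It arrives at 62 participants, or 78 after allowing for 20% drop-out.

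**The concern.** The primary analysis and the sample size do not describe the same test. The sample size belongs to one AUC tested once. The primary analysis concerns a technique that produces several indices, any of which could be presented as the answer.

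If several are examined at P<.05 and the best is reported, two things happen. The false-positive rate for the primary question exceeds 5%, and the selected AUC is biased upwards. The Discussion intends the results to support a preoperative predictive model, so an index picked by chance could be carried into clinical use. Once outcomes have been seen, no choice of primary index can be shown to have been made independently of them.

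**Working it through.** **Inputs.** From the protocol article: 2 muscles, 3 colours and 4 quadrants (Image part of section 2.5); P<.05 (section 2.7); alpha 0.05, type II error 0.2, AUC 0.7, ratio 1, N 62 and 78 (section 2.8). Assumed, because the article does not give them: null AUC 0.5, a two-sided test, and the correlations between indices.

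**1. Reproducing 62 and 78.** With the Hanley-McNeil large-sample variance V(A) = A/(2−A) + 2A²/(1+A) − 2A²:

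- V(0.5) = 0.1667, square root 0.408
- V(0.7) = 0.1349, square root 0.367
- n per group = [(1.960 × 0.408 + 0.842 × 0.367) / 0.2]² = 30.8, so 31 per group and 62 in total
- 62 / 0.8 = 77.5, so 78

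The stated figures therefore reproduce for one AUC, 0.7 against 0.5, at two-sided 0.05 and 80% power. The finite-sample form of the same variance gives 64; one-sided versions give 42 to 50.

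**2. Number of indices.** 2 × (3 + 4) = 14. This is the maximum that the text allows.

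**3. Link to the group comparison.** The Mann-Whitney U statistic divided by n1 × n2 is the AUC, so that test is a test of AUC = 0.5. If the elastography measures count among the continuous variables of section 2.7, each is tested against reparability at P<.05, whichever ROC curves are later shown.

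**4. Chance of at least one P<.05 when no index has value.** For 14 independent indices it is 1 − 0.95^14 = 0.512; for 4 it is 1 − 0.95^4 = 0.185. For correlated indices, a simulation with 31 against 31, rank tests and 20,000 replicates gives:

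| Common correlation (assumed) | At least one P<.05, 14 indices | Mean best AUC, direction chosen after the data |
|---|---|---|
| 0 | 51% | 0.65 |
| 0.3 | 44% | 0.64 |
| 0.5 | 37% | 0.64 |
| 0.7 | 26% | 0.62 |
| 0.8 | 20–21% | 0.61 |
| 0.9 | 15% | 0.60 |

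High correlation within each muscle-and-method block (0.7 to 0.9) and lower correlation between blocks (0 to 0.5) gives about 27% to 38%. With four indices the range is about 9–10% (correlation 0.9) to 18% (correlation 0).

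**5. Baseline for the best AUC.** At 31 against 31 the null standard deviation of the AUC is √[63 / (12 × 31 × 31)] = 0.074. One useless index with its direction chosen afterwards averages 0.5 + 0.798 × 0.074 = 0.56. Selection among 14 thus adds about 0.04 to 0.09.

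**6. Power.** Unadjusted, each index with a true AUC of 0.7 keeps about 80% power at 62. Under Bonferroni over 14 the critical value is 2.914, and power is Φ[(0.2 × √31 − 2.914 × 0.408) / 0.367] = Φ(−0.21) = 42% (41% with the finite-sample variance). Restoring 80% would need 114 evaluable participants, or 114 / 0.8 = 142.5, so 143 enrolled.

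**The case against.** The article nowhere says that 14 ROC curves will be tested. Section 2.7 gives no number of curves, its list of elastography outcomes mentions each colour and SWV but not quadrants, and the Discussion leaves room for a combined model. Anything from one curve to 14 fits the text. This stands, so 14 must be read as a maximum.

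A reader might infer that a chance finding is likely. That needs near-independence. Quadrants of one region and colours from one image are probably correlated, and the figure then falls below one half. It still stays well above 5% throughout the range examined, even with four indices.

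A reader might also infer that the stated 80% power is lost. It is not: unadjusted testing keeps it for each index. The 41–42% arises only under a Bonferroni correction that the protocol does not propose, so inflated error and lost power cannot both be charged to the same plan.

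Nor would a useless index often reach the 0.7 that section 2.8 treats as acceptable. With direction chosen afterwards, the best of 14 null AUCs does so in about 8%, 7% and 4% of studies at correlations 0, 0.5 and 0.8.

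Finally, this is a condensed article on an observational study, and multiplicity rules are often left to an analysis plan. That is fair for the handling of secondary indices. It does not cover the choice of the primary index, because the sample size that the article does state presupposes that choice.

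**Conclusion.** The point holds in limited form. The primary analysis fixes no index among up to 14 and no multiplicity rule, while 62 and 78 rest on a single AUC test, so the stated 5% error does not cover the primary question. The inflation is to about 15–50% if all 14 are tested, and about 9–18% if four are. Both ranges rest on assumed common correlations of 0.9 to 0, equal groups of 31 and no true signal. A selected null AUC would average about 0.60–0.65 instead of about 0.56. The documents do not support saying that 14 tests are planned, that a false positive is more likely than not, or that power per index is below 80%.

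**What to change.** In section 2.7, before any outcome is seen, name one primary elastography index or composite and the direction in which it is expected to predict reparability. One muscle's SWV averaged over its four quadrants would serve as an example; the investigators should choose the muscle on prior grounds, since nothing in the article settles it. Test its AUC against 0.5 at two-sided 0.05. That is the test for which 62 gives 80% power, so 62 and 78 stand.

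Label all other indices either secondary, with Holm adjustment, or exploratory, with confidence intervals only.

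The cost is a few sentences and no extra participants. The downside is that a signal confined to a non-primary index can only be called secondary or exploratory. The alternative of keeping all 14 as co-primary under Bonferroni would need 143 enrolled to retain 80% power for each index.
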